### Laboratory and other investigations

All laboratory results will be filled into a form marked with the participant’s study ID and kept in confidential storage for entering of follow-up results.

Depending on the tests to be performed, different tubes will be used for blood collection:○ To obtain serum, whole blood will be collected through venipuncture in plain vacutainer tubes (or equivalent) allowed to clot and serum separated after centrifugation. Venous blood specimen will be drawn to enable analysis of Zika IgM and IgG antibodies in serum and for the ZIKV Ag assay.○ To obtain plasma whole blood will be collected through venipuncture in a vacutainer tube containing EDTA, allowed to stand or centrifuge to separate plasma.○ For cytokine determination the correct anticoagulant should be heparin.

### Screening

**Visit 0**: blood and urineRapid pregnancy testBlood: 2 tubes of 5 mL without anticoagulant (SST tube) for ZIKV RT-PCR and biochemistry and 1 tube of 5 mL EDTA for haematologyUrine: 10 to 50 ml in universal urine analysis tube for ZIKV RT-PCR

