#### Secondary objectives

To analyse the presence and duration of ZIKV in bodily fluids amongst male and female adults aged 18 years and above over a 12 months period.To analyse the persistence of other markers (ZIKV RNA, IgM, IgG, antigen) of ZIKV infection in bodily fluids amongst male and female adults aged 18 years and above over a 12 months period.To explore potential relation between host and environmental factors as well as co-infections - dengue, chikungunya, HIV, syphilis, HBV, HCV, Oropouche virus (Bunyavirus), Mayaro virus and Yellow Fever (check immunization status) - on the duration of the persistence of the virus in body fluids. HIV, syphilis, HBV and HCV tests will be provided by the National AIDS control programme. The algorithms used by the programme for testing and treatment will be used.To assess the proportion of asymptomatic infections among household/sexual contacts to infected cases.To assess the possibility of reinfection or reactivation of the ZIKV cases over the study period.To describe concordance between RT-PCR test results, neutralizing antibodies, virus isolation, antigen results, and specific ZIKV antibody responses in these fluids.

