## Methods/design

### Study design

This is a prospective observational cohort study. After signing a screening consent, male and female potential study participants presenting rash compatible with ZIKV infection in collaborating clinics will be tested for the presence of ZIKV in blood and urine. The following day, after providing informed consent for enrolment, those found to be RT-PCR positive for ZIKV infection, fulfilling all inclusion criteria will be enrolled and subject of regular collection of body fluids over a period of 12 months according to a pre-established schedule. Household/sexual contacts will be screened at the reference centers where the index case was diagnosed or if preferable at their household, and recruited following the same criteria. The standard care will be provided to all participants.

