### Index case - enrolment

**Enrolment inclusion criteria**
○ Presenting RT-PCR test positive for ZIKV in blood and/or urine specimens collected during screening○ Having given consent to provide all body fluid collection, as appropriate, according to the testing schedule

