### Admission procedure

#### Index case

**Screening visit (visit 0)**

As a first step during the screening visit, the study nurse will explain the study to potential participants. Pictograms depicting the collection of different body fluids will be used for facilitating the communication between them.After ensuring the participant understood the information provided and that all their questions have been answered, an initial informed consent will be signed. The informed consent will state that the specimens will be collected during screening and after enrolment, when applicable, and that participation in the full study will only occur should a positive result for ZIKV infection be found in the patient’s blood and/or urine. A short questionnaire (Screening questionnaire) with basic socio-demographic data will be applied. This is the initial part of a more detailed questionnaire that will be completed if tests yield positive results and the individual continues in the study.Specimen collection will be completed in a secure, private space in the study clinic using appropriate infection control precautions. Blood and urine will be tested using RT-PCR.The participant will receive explanation about the next steps. These steps will depend on whether the ZIKV RT-PCR testing in blood or urine turn out to be positive or negative.The participant will also receive information on the communication occurring with his/her household contacts and/or sexual partners. The index case will be informed of the necessity to visit the household, or receiving the household members/sexual partner at the clinic for explanation about the study, informed consent, short questionnaire, and collection of specimens at the clinic at the same or following day of the result delivery.The laboratory results for RT-PCR of blood and urine of the index case should be available within 24–48 h after specimens arrived at the laboratory, regardless of the day of the week.An appointment will be made with the index case for the following day for delivering of the test results (visit 1).At each study site, participants will receive a financial amount to cover the costs of their transport and a meal. This will happen at each study visit. Individuals not willing to attend the collaborating clinic will be offered the alternative of being visited at home by a study nurse at their convenience.

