b)**Enrolment visit (Visit 1):** Laboratory results delivery - the day results for blood and urine specimens are available. The test result will be delivered to the participant by the study nurse at the enrollment site.
Negative RT-PCR for ZIKV in blood and urine

For individuals whose ZIKV RT-PCR tests performed on urine and blood returned negative, management will be done according to regular procedures and they will be referred back to the initial clinic where they were seen in the first place.Positive RT-PCR for ZIKV in blood or urine

Individuals whose RT-PCR tests performed on blood or urine are positive will be considered as index cases. The next steps will be the following:○ The nurse will explain in details what the full enrolment in the study entails and ask for an informed consent for the index case to continue in the full study.○ A detailed questionnaire will be applied (Enrolment questionnaire).○ The nurse will proceed with the specimen collection of all body fluids discussed previously with the index case, including new blood and urine specimens.○ The specimen collection schedule will proceed according to the time frame and intervals shown in Table 1.○ Specimens collected will be noted on forms.○ The nurse will also discuss with the index case the invitation of the household contacts/sexual partners to the study.

**Table 1 Tab1:** Time frame for collection of specimens

Time	Recruitment visit index case	Recruitment visit household member	Sample collection		
Visit 0	Sample collection	–	Blood and urine		
Visit 1 – inclusion visit	Visit 0 + 2 days				
	RT-PCR Results				
	-RT-PCR positive: individuals start follow up	Invitation to attend the clinic or household visit by the nurse (Blood and urine)			
	-RT-PCR negative: individuals are not included in the study				O
Visit 2	Visit 1 + 2 days	Visit 1 + 3 days			T
Visit 3	Visit 1 + 4 days	Visit 1 + 5 days			H
Visit 4	Visit 1 + 10 days	Visit 1 + 11 days	B		E
Visit 5	Visit 1 + 20 days	Visit 1 + 21 days	L		R
Visit 6	Visit 1 + 30 days	Visit 1 + 30 days	O	+	
Visit 7	Visit 1 + 60 days	Visit 1 + 60 days	O		F
Visit 8	Visit 1 + 90 days	Visit 1 + 90 days	D		L
Visit 9	Visit 1 + 120 days	Visit 1 + 120 days			U
Visit 10	Visit 1 + 150 days	Visit 1 + 150 days			I
Visit 11	Visit 1 + 180 days	Visit 1 + 180 days			D
Visit 12	Visit 1 + 210 days	Visit 1 + 210 days			S
Visit 13	Visit 1 + 240 days	Visit 1 + 240 days			
Visit 14	Visit 1 + 270 days	Visit 1 + 270 days			
Visit 15	Visit 1 + 300 days	Visit 1 + 300 days			

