### Enrolled patients

**Visit 1 and following visits** – for RT-PCR positive patients (enrolled). The steps below will be followed for specimen collection of specific body fluids:

Pregnancy test: rapid urine test.

Diabetes screening: blood drop – glucometer tests

BloodVisit 1, 4, 6–17○ Brazil: HIV, syphilis, hepatitis B and C; RT-PCR for ZIKV, Dengue, Chikungunya. Immune response: IgG, IgM, ZIKV antigen, serological screen for exanthematic virus, Oropouche virus (Bunyavirus) and Mayaro virus, Yellow Fever (check immunization status);○ Walter Reed: PRNT, micro neutralization, flow based neutralization, T cells assays, cross reactions;○ 2 × 10 mL SST tubes should optimally be collected;○ 1 × 10 mL heparin tube.Visit 2, 3, 5○ 1 × 10 mL SST
Urine (for ZIKV RT-PCR; antigen; HCG; virus isolation)
20–50 mL of urine will be collected in a screw top urine container1 aliquot of 2 mL to be processed immediately for RT-PCR1 aliquot of 2 mL of urine will be frozen at − 70 °C for antigen3 aliquots of 2 mL will be frozen for future studies

Considering that for the following fluids is not possible to predict the final volume that will be available after collecting, it is important to consider that is necessary to have at least 500 μl for RT-PCR and serology (if applicable) and an additional 500 μl to be kept frozen at − 70 °C for future studies.

For the following specimen types, one fresh aliquot should be processed for RT-PCR for ZIKV and 2 aliquots should be stored frozen at − 70 °C for Ag test and culture:b)Oral fluids (saliva, crevicular fluid)c)SemenEjaculateCollected in a screw top urine containerd)Sweate)Tearsf)Vaginal secretiong)Menstrual bloodh)Breast milki)Rectal secretion

Note: Participants will be asked for consent their specimens to be used for future research. Specimens of consenting individuals will be kept at − 70 °C. Specimens that test positive by RT-PCR will also be processed for culture/viral isolation.

WHO will provide guidance on assay selection. Laboratories from different sites will be using the same assays, reagents and equipment.

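### Dengue and chikungunya RNA is first tested one or two days after the screening specimens that define ZIKV infection, so some acute co-infections may be missed by RT-PCR

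*Protocol article*

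**What the plan says.** **Specimen that defines ZIKV infection.** The enrolment inclusion criterion is "Presenting RT-PCR test positive for ZIKV in blood and/or urine specimens collected during screening".

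**What is run on that specimen.** Under Laboratory and other investigations, Screening, the Visit 0 serum is "2 tubes of 5 mL without anticoagulant (SST tube) for ZIKV RT-PCR and biochemistry", the EDTA tube is for haematology, and the urine is "10 to 50 ml in universal urine analysis tube for ZIKV RT-PCR". No dengue or chikungunya assay is listed at Visit 0.

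**Where the other two viruses enter.** Under Enrolled patients, the blood panel for Visits 1, 4 and 6–17 includes "RT-PCR for ZIKV, Dengue, Chikungunya". The enrolment visit description says that all body fluids are collected at that visit, "including new blood and urine specimens", so Visit 1 is a separate draw.

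**How far apart the draws are.** Study design has "The following day, after providing informed consent for enrolment, those found to be RT-PCR positive for ZIKV infection" being enrolled. The screening visit text also books the results appointment for the following day, although results "should be available within 24–48 h after specimens arrived at the laboratory". Table 1 puts Visit 1 two days after Visit 0.

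**What co-infection is used for.** A secondary objective is "To explore potential relation between host and environmental factors as well as co-infections" and the duration of persistence. The Data analysis plan lists the rate of dengue and chikungunya among its measures of interest and both viruses among the host factors for persistence. Under Confirmation of recent ZIKV infection, the IgM and PRNT90 algorithm is required when nucleic acid of ZIKV is found together with that of dengue or chikungunya.

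**The concern.** Visit 0 is the earliest and most acute sample for each participant, and it is not tested for the two arboviruses whose co-infection is of interest. If dengue or chikungunya RNA is present at Visit 0 and gone by Visit 1, RT-PCR will not find it. The next listed RT-PCR for these viruses is Visit 4, ten days after Visit 1.

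Three things follow. The reported co-infection rate is too low. The co-infected group for the persistence analysis is smaller than it need be. A participant who carried both RNAs at screening does not enter the dual-nucleic-acid confirmation step. The article lists its assays visit by visit, so this is a stated choice and not a detail lost in condensing the protocol. A later analysis plan cannot recover the result of a specimen that was neither tested nor kept.

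**Working it through.** The plan states no figure for this point, so there is nothing to reproduce. The sequence of tests comes from the text; the size below rests on assumptions.

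**Step 1. Order of events.**
- Visit 0: ZIKV RT-PCR on blood and urine. This defines infection.
- Visit 1, one day later (Study design, screening visit text) or two days later (Table 1): new draw, with the first dengue and chikungunya RT-PCR.
- Visit 4 (Visit 1 + 10 days), then Visits 6–17: repeats. Listed time points: 1 + 1 + 12 = 14.

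**Step 2. Share lost in the gap.** Assumptions, because the article gives no dengue or chikungunya RNA duration: presentation day p is equally likely to be 0, 1, 2, 3, 4 or 5 after onset, and RNA is detectable up to day D, with D from 3 to 7. A co-infection is detectable at Visit 0 if p ≤ D. It is lost with a gap of g days if also p + g > D.

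| D | Days detectable at Visit 0 | Lost, g = 1 | Lost, g = 2 |
|---|---|---|---|
| 3 | 0–3 (4 days) | 1/4 = 25% | 2/4 = 50% |
| 4 | 0–4 (5 days) | 1/5 = 20% | 2/5 = 40% |
| 5 | 0–5 (6 days) | 1/6 = 17% | 2/6 = 33% |
| 6 | 0–5 (6 days) | 0/6 = 0% | 1/6 = 17% |
| 7 | 0–5 (6 days) | 0/6 = 0% | 0/6 = 0% |

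**Step 3. A second model as a check.** Let the RNA time remaining at Visit 0 be exponential with mean m days. The share lost is 1 − exp(−g/m). For m from 2 to 7 days this is 39% to 13% with g = 1 and 63% to 25% with g = 2. The exponential form has no fixed end to the detectable window, so it never reaches zero.

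**Step 4. Effect on the co-infection rate.** Take 1300 participants (650 men and 650 women), an assumed true co-infection share π and a lost share f. The observed share is π(1 − f). At π = 5%, the true count is 65.
- f = 25% (largest one-day value in Step 2): 65 × 0.75 ≈ 49.
- f = 50% (largest two-day value in Step 2): 65 × 0.50 ≈ 33.
- f = 13% to 63% (range from Step 3): 4.4% to 1.9%, or about 57 to 24.

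**Step 5. Effect on the association.** If RNA alone defines co-infection, the share of the apparently ZIKV-only group that is co-infected is s = πf / (1 − π + πf). If the missed cases resemble the detected ones in persistence, a risk difference shrinks by the factor 1 − s.
- Smallest case, π = 2%, f = 13%: s = 0.0026 / 0.9826 = 0.3%.
- Largest case, π = 10%, f = 63%: s = 0.063 / 0.963 = 6.5%.

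Dilution from missed cases is therefore at most about 7% over the assumed range.

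**Step 6. Value of the late repeats.** With a 3- to 7-day detectable window and tests 30 days apart, a new infection after day 30 is caught with probability 3/30 to 7/30, or 10% to 23%.

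**The case against.** A reader might infer that the missed patients are coded as ZIKV-only. The article does not say so. It gives no coding rule for co-infection, and neither the secondary objective nor the Data analysis plan ties co-infection to RNA. Only the confirmation rule is tied to nucleic acid.

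There is also a non-RNA route. The panel for Visits 1, 4 and 6–17 lists IgG, IgM, a serological screen for exanthematic virus, PRNT and micro neutralization. Site laboratories were chosen partly for neutralising antibody tests specific to dengue and chikungunya. Paired samples could show a recent infection after its RNA has cleared. This objection stands in part. The safeguard is uncertain, because dengue and chikungunya are not named as serology targets, and the abstract makes PRNT conditional on simultaneous ZIKV and dengue positivity while the visit panel lists it without that condition.

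A reader might also infer that the two statuses always come from different days. That goes too far. All three RT-PCRs are run on the same Visit 1 blood, and the confirmation rule does not require both RNAs in one specimen. A ZIKV positive at Visit 0 with a dengue positive at Visit 1 could still trigger it.

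A stronger claim of serious dilution of the persistence association is not supported either (Step 5). Nor can much be made of later infections being counted as co-infection, since monthly testing would catch few of them (Step 6). The sample size section calls the subgroup analyses exploratory.

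Finally, the onset-based clock in Step 2 does not fit asymptomatic contacts, and the assumed windows include a loss of zero.

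**Conclusion.** The point holds in a limited form. As written, dengue and chikungunya RT-PCR starts one or two days after the specimens that define ZIKV infection. Co-infections whose RNA clears in between may be missed or misclassified unless serology defines co-infection, and they would not trigger the dual-nucleic-acid confirmation.

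Under the windows assumed in Step 2, the loss is 0–25% for a one-day gap and 0–50% for a two-day gap. It cannot be narrowed from the document, which states neither RNA duration nor co-infection prevalence. The consequences are an understated co-infection rate and fewer co-infected participants for an exploratory analysis. Enrolment and the primary 12-month persistence rate rest on ZIKV results, so the missed co-infections do not affect them. This is an inexpensive improvement to consider, not a flaw that threatens the study's main aim.

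**What to change.** 1. In the Screening part of the laboratory section, state that an aliquot of Visit 0 serum is kept. The article does not say this now; it assigns those tubes to ZIKV RT-PCR and biochemistry.
2. Run dengue and chikungunya RT-PCR on that aliquot for everyone enrolled, either in addition to Visit 1 or in exchange for one late time point.
3. State which test and specimen define co-infection. A workable definition of baseline co-infection is dengue or chikungunya RNA at Visit 0 or Visit 1, with later positives kept apart from it. If serology is to contribute, name dengue and chikungunya as targets.
4. Reconcile the one-day interval in the Study design and screening visit text with the two-day interval in Table 1.

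**Cost.** Two extra assays per enrolled participant, or none if one of the 14 listed time points is dropped, plus an aliquot of serum already drawn. No visit or blood draw is added. Testing Visit 0 serum removes the loss between Visit 0 and Visit 1; RNA that cleared before Visit 0 would still be missed.

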### Enrolled patients

**Visit 1 and following visits** – for RT-PCR positive patients (enrolled). The steps below will be followed for specimen collection of specific body fluids:

Pregnancy test: rapid urine test.

Diabetes screening: blood drop – glucometer tests

BloodVisit 1, 4, 6–17○ Brazil: HIV, syphilis, hepatitis B and C; RT-PCR for ZIKV, Dengue, Chikungunya. Immune response: IgG, IgM, ZIKV antigen, serological screen for exanthematic virus, Oropouche virus (Bunyavirus) and Mayaro virus, Yellow Fever (check immunization status);○ Walter Reed: PRNT, micro neutralization, flow based neutralization, T cells assays, cross reactions;○ 2 × 10 mL SST tubes should optimally be collected;○ 1 × 10 mL heparin tube.Visit 2, 3, 5○ 1 × 10 mL SST
Urine (for ZIKV RT-PCR; antigen; HCG; virus isolation)
20–50 mL of urine will be collected in a screw top urine container1 aliquot of 2 mL to be processed immediately for RT-PCR1 aliquot of 2 mL of urine will be frozen at − 70 °C for antigen3 aliquots of 2 mL will be frozen for future studies

Considering that for the following fluids is not possible to predict the final volume that will be available after collecting, it is important to consider that is necessary to have at least 500 μl for RT-PCR and serology (if applicable) and an additional 500 μl to be kept frozen at − 70 °C for future studies.

For the following specimen types, one fresh aliquot should be processed for RT-PCR for ZIKV and 2 aliquots should be stored frozen at − 70 °C for Ag test and culture:b)Oral fluids (saliva, crevicular fluid)c)SemenEjaculateCollected in a screw top urine containerd)Sweate)Tearsf)Vaginal secretiong)Menstrual bloodh)Breast milki)Rectal secretion

Note: Participants will be asked for consent their specimens to be used for future research. Specimens of consenting individuals will be kept at − 70 °C. Specimens that test positive by RT-PCR will also be processed for culture/viral isolation.

WHO will provide guidance on assay selection. Laboratories from different sites will be using the same assays, reagents and equipment.

### Confirmation of recent ZIKV infection

Laboratory confirmation of recent ZIKV infection will comprise:Presence of ZIKV RNA or antigen in serum or other specimens (e.g. oral fluid, tissues, urine, whole blood); orWhen the patient is found to have nucleic acid specific for ZIKV as well as chikungunya or dengue, confirmatory testing of serum will be required. ZIKV infection will be confirmed when: IgM antibody against ZIKV positive and PRNT90 for ZIKV with titre ≥20 and ZIKV PRNT90 titre ratio ≥ 4 compared to other flaviviruses; and exclusion of other flaviviruses.Virus culture will be performed in order to determine whether a given body fluid specimen has live virus. The results of the virus isolation will be reported to the correspondent study nurse.

### Provision of results to participants

All laboratory results will be filled into a form marked with the participant’s study ID and kept in confidential storage for entering of follow up results.

### Genotyping/selected full-length sequencing

Additional genomic analysis will be performed on a subset of positive samples by full-length sequencing methods. Whole genome sequencing and cognate viral load measures will be explored. Confirmatory follow-on procedures including real-time quantitative PCR will be performed as necessary, preferably with commercial reagents or alternatively those laboratory developed assays adapted from the literature. Viruses may be obtained by co-culturing with activated peripheral blood mononuclear cells (PBMCs), if other molecular methods for virus sequence determination fail.

### Lymphocyte Polyfunctional studies and Immunophenotyping

Assays for cellular and humoral immune responses will be measured with the specimens stored during the study and will be determined based on the level of technology at the time. CD4+ and CD8+ T cells, B cells and NK cellular responses may be evaluated by a variety of assays including multi-parameter flow cytometry, intracellular cytokine staining and ELISPOT assays. Cytokine levels and inflammatory biomarkers may be measured by sandwich-ELISA method using validated commercial cytokine kits or alternative methods such as Luminex or other multiplexed platforms. Further advances in immunologic assays will occur and may be utilized. Immunophenotyping according to multiple lineage and differentiation markers may be carried out depending on the availability and salience of cutting edge assays. Additional cell types may also be evaluated by flow cytometry. Additionally, single cell immunophenotyping analysis, single cell sorting, antibody Fc-effector profiling and functionality assays and antibody cloning may also be performed.

